
### 2.2. Experimental Vignettes

The four vignettes describe distinct configurations of AI involvement in facial reconstructive surgical planning, varying both the AI’s task (imaging analysis, decision support, outcome simulation, autonomous planning) and the surgeon’s level of supervision (Table 1). Each configuration corresponds to a capability documented in the current literature: anatomical structure analysis from CT [6,8], algorithmic generation of candidate surgical plans [9], three-dimensional simulation of postoperative facial appearance [12,13], and highly autonomous planning of the kind anticipated by surgical-autonomy frameworks [14,15]. All vignettes open with an identical premise (the respondent needs facial reconstructive surgery following an injury) and are written in parallel second-person wording of comparable length and reading difficulty, so that scenario content—not framing—drives differences in responses. Because the four configurations differ in what the AI does as well as in how much the surgeon decides, a perceived difference between them could in principle reflect technical sophistication rather than autonomy. Three features are intended to keep the two apart. First, every vignette closes by stating explicitly how the final surgical plan is reached and by whom. In Scenarios A–C, a single clause of parallel construction names the surgeon as the decision-maker (making all decisions, choosing among the proposed options, or deciding the final plan after reviewing the simulations); in Scenario D, the closing sentences state that the surgeon reviews the AI’s plan but rarely modifies it. What varies is therefore the decisional locus, not the computational task. Each comprehension check is built on that same feature: the decision-maker in Scenarios A and B; the role of the system in Scenario C (whose decisional clause is functionally equivalent to Scenario B’s, so that the role is what distinguishes the two); and the origin of the plan actually followed in Scenario D. Second, the vignettes are matched on the quantity of technical detail supplied—one sentence describing the system’s input and output in each case—so that described sophistication does not rise in step with autonomy. Scenario C specifies a generative three-dimensional simulation, computationally the most elaborate output in the set, yet leaves the decision entirely with the surgeon; Scenario D describes a comparatively conventional optimization whose distinguishing feature is decisional rather than technical. Third, two manipulation checks follow every scenario: MAN1, perceived control of the AI over the final decision, and MAN2, perceived technical sophistication of the system. The manipulation is treated as valid only if MAN1 orders the scenarios as intended; MAN2 verifies that sophistication does not itself increase monotonically with autonomy and enters a pre-specified sensitivity analysis as a covariate, so that the autonomy effect can be estimated with perceived sophistication held constant (Section 2.9.1). The full vignette texts are provided in Appendix A.

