### 2.5. Sample Size and Power

Sample size is justified a priori following current recommendations [70], with all calculations derived analytically from noncentral *F*, t, and chi-square distributions at a two-tailed significance threshold of α = 0.05 and a target power of 1 − β = 0.80, reproducible in G*Power 3.1 (“ANOVA: Repeated measures, within factors”) and consistent with recent tutorials on power analysis for repeated-measures designs [63]. The primary test is a repeated-measures ANOVA (four within-subject levels) on each composite score. Assuming a correlation between repeated measurements of ρ = 0.50 (a typical value for repeated attitudinal ratings, to be verified in the pilot), the minimum sample is 24 participants for medium effects (*f* = 0.25) and 138 for small effects (*f* = 0.10); under the conservative assumption ρ = 0.30, these become 32 and 193, respectively. The minimum analyzable threshold is therefore set at *N* = 140 valid participants, sufficient to detect even small between-scenario effects under realistic conditions. Because these thresholds depend on ρ, an adaptive rule is pre-registered for the case in which the pilot estimate falls outside the assumed ρ = 0.30–0.50 range. The pilot returns $\hat{\rho }$ with a 95% confidence interval, and every threshold is recomputed at its lower bound, ρ_L_, which is the conservative choice. The number of valid participants required to detect *f* = 0.10 at power 0.80 is 274, 247, 220, 193, 165, and 138 for ρ_L_ = 0, 0.10, 0.20, 0.30, 0.40, and 0.50, respectively; an intermediate ρ_L_ is rounded down to the nearest tabulated value, so that the rule is fully determined in advance for any estimate the pilot can return. Two consequences follow. The recruitment target does not change because the requirement is a decreasing function of ρ and reaches only 274 in the theoretical worst case of ρ_L_ = 0; *N* = 300 preserves power ≥0.80 against small between-scenario effects for every value ρ can take, and the target is in any case set by the person-level analyses described below, which do not depend on ρ. The analytic floor does change: it is redefined as the value tabulated above for the observed ρ_L_, so that it remains at the pre-specified *N* = 140—rounded up from 138—only when ρ_L_ ≥ 0.50 and rises to 165, 193, 220, 247, or 274 as ρ_L_ falls to 0.40, 0.30, 0.20, 0.10, or 0. A ρ_L_ below 0.10 would in addition indicate that the composites are unstable across repetitions rather than that participants are inconsistent, and would therefore also trigger re-inspection of pilot reliability and of the measurement-invariance assumptions before the main study is launched. Any application of this rule, and the $\hat{\rho }$ that triggered it, will be recorded in the pre-registration and reported in the results article.

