
### 2.8. Pilot Study and Instrument Validation

The instrument will be validated in a pilot study (*N* = 50, not included in the main sample, allocated 1:1 to the ascending sequence A → B → C → D and to its exact reverse D → C → B → A) before the main study is launched. The pilot will estimate (i) internal consistency—Cronbach’s α and McDonald’s ω with 95% confidence intervals for each three-item composite, computed separately per scenario, against a threshold of ≥0.70, with ω reported alongside α in line with current psychometric guidance [73]; with three items per construct, α ≥ 0.70 requires a mean inter-item correlation of only $\bar{r}$ ≥ 0.44 under the generalized Spearman–Brown relation (Figure 2), a realistic requirement for parallel items; (ii) inter-item correlations (flagged at r > 0.90 for redundancy or r < 0.20 for heterogeneity) and corrected item-total correlations (threshold ≥ 0.40), plus the correlation between repeated measurements, reported with a 95% confidence interval, to verify the ρ ≈ 0.50 planning assumption and, where it is not met, to trigger the adaptive sample-size rule of Section 2.5; (iii) the factor structure of the nine response items, via exploratory factor analysis (principal-axis extraction, oblique rotation, sampling adequacy KMO ≥ 0.70, Bartlett’s test of sphericity, parallel analysis as the retention criterion)—an anticipated risk is that acceptability and trust items form a single factor, in which case the two constructs will be merged into a single “trust–acceptance” score and the analysis plan adjusted transparently before pre-registration, with this decision taken exclusively on pilot data; (iv) first-attempt comprehension-check pass rates per scenario (threshold ≥ 70%); (v) manipulation validity—MAN1 scores must order the scenarios from A to D in both pilot arms, while MAN2 (perceived technical sophistication) must not increase monotonically with autonomy; if it does, the vignettes will be reworded to equalize the described sophistication of the systems and the check repeated before pre-registration; (vi) fatigue—perceived difficulty (DIF1) and section-wise drop-out across serial positions in both arms; (vii) cognitive interviews with 5–8 participants to identify confusing wording, probing in particular whether RES1–RES6 are read in the intended senses of moral answerability, outcome-independent accountability, and legal fault (Section 2.6); and (viii) a first bound on order effects—the two pilot arms are compared on the three composites and on MAN1 by a scenario × order mixed ANOVA (*n* = 25 per arm; minimum detectable interaction *f* = 0.17 at ρ = 0.50), which can exclude medium-to-large order artifacts but not small ones, the definitive test being the main-study interaction. The four-sequence randomizer used in the main study is implemented in the same pilot build. Because the pilot itself exercises only two of the four arms, the randomizer is verified there by simulated allocation, which also confirms that the allocated sequence and the serial position of each scenario are stored correctly. A ninth objective is included: (ix) the keying and dimensionality of the four general-attitude items (G1–G4), since G3 is a caution item that the present scoring treats as positively keyed while G2 and G4 are reversed; the scoring rule for that block is fixed on pilot data before pre-registration, and if the four items do not form a single interpretable dimension they will enter the person-level analyses individually rather than as a composite. Because a sample of 50 is at the lower limit for stable factor solutions, the pilot EFA is treated as provisional: the factor structure will be re-examined by confirmatory factor analysis on the main sample (*N* = 300), with acceptable fit defined a priori as CFI/TLI ≥ 0.95, RMSEA ≤ 0.06, and SRMR ≤ 0.08. Because the same nine items are answered four times, longitudinal measurement invariance across the four scenario repetitions (configural, metric, and scalar) will also be tested on the main sample; at least partial scalar invariance is required for the between-scenario comparison of composite means, and any non-invariant item will be reported and handled by partial-invariance modeling. Pilot results will be reported in the methods section of the results article.

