
### 2.9. Statistical Analysis

#### 2.9.1. Primary Analyses

Each composite score (acceptability, trust, perceived risk) will be analyzed by a mixed repeated-measures ANOVA, with autonomy level (four scenarios) as the within-subjects factor and presentation sequence (four Williams sequences) as the between-subjects factor. The Greenhouse–Geisser correction will be applied when Mauchly’s test indicates a sphericity violation (Huynh–Feldt for ε between 0.75 and 1), and the multivariate approach (Pillai’s criterion) will be reported in parallel as a sphericity-robust check. H1 and H2 will be tested with within-subjects trend contrasts across the autonomy gradient. Because acceptance need not fall in a straight line, the complete set of orthogonal polynomial contrasts—linear, quadratic, and cubic—is pre-specified, and each is reported together with the proportion of the omnibus effect it accounts for. A purely linear profile leaves the quadratic and cubic components negligible, whereas a step between two adjacent levels appears as a large linear component accompanied by a substantial quadratic or cubic one. Because every monotone step is linear-dominant, the polynomial decomposition establishes departure from a straight line but cannot by itself locate the break; the break is identified only from the Holm-corrected adjacent-pair contrasts (A–B, B–C, C–D). A quadratic-dominant profile with a small linear component would instead indicate a non-monotone pattern, which the hypotheses do not predict and which would be reported as such. A non-monotonic or threshold pattern will be reported as such rather than summarized by the linear trend alone. Post hoc comparisons use dependent-samples *t*-tests for the six scenario pairs with Holm’s sequential correction, applied within each hypothesis-defined family of tests in line with current guidance on multiplicity control [74]. Effect sizes will be reported as partial η^2^ for omnibus tests and Cohen’s dz for pairwise comparisons, with 95% confidence intervals, following effect-size-centered reporting recommendations [64]. Assumption checks include graphical inspection of difference-score distributions; as a distributional robustness analysis, the Friedman test with Holm-corrected Wilcoxon signed-rank pairwise comparisons will be reported alongside each primary test—supplemented by ordinal (cumulative-link) models as sensitivity analyses for the Likert-based outcomes [71]—and the concordance of parametric and nonparametric conclusions stated explicitly. Order dependence is tested directly as the scenario × sequence interaction; a non-significant interaction, together with equivalence of the four sequence-specific profiles, supports pooling across sequences. Independently of that test, the autonomy effect is re-estimated from a linear mixed model with random intercepts per participant and additive fixed effects of autonomy level and serial position (1–4). The Williams square renders this model identified, so the estimate is adjusted for arbitrary—not merely linear—serial-position and fatigue effects, while first-order carry-over is balanced by the design rather than modeled; position-adjusted and unadjusted estimates are reported side by side, and any material divergence between them is treated as evidence of an order artifact and interpreted accordingly. Perceived difficulty (DIF1) and perceived technical sophistication (MAN2) are each added as time-varying covariates in further sensitivity models, addressing fatigue and the possibility that responses track the apparent complexity of the system rather than its autonomy. Finally, between-person heterogeneity in response profiles is examined by adding a random slope for the linear autonomy contrast and testing the improvement in fit by a likelihood-ratio test; a substantial random-slope variance indicates that an average trajectory conceals distinct response patterns and licenses the exploratory typology described in Section 2.9.2. Because a non-significant test is not evidence of absence, a smallest effect size of interest of *dz* = 0.20—the value detectable at the Bonferroni bound for the six pairwise contrasts at *N* = 300—is fixed in advance, and equivalence testing by two one-sided tests against that bound is reported alongside every null pairwise result, so that any claim that two adjacent scenarios do not differ rests on an equivalence test rather than on the absence of significance.

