## 3. Expected Results

Based on the algorithm-aversion and trust studies [19,37,38], we expect acceptability and trust to decline—and perceived risk to rise—across the autonomy gradient from Scenario A to Scenario D, with the largest drop anticipated at the transition to autonomous planning (Scenario D), where the surgeon’s corrective role is described as residual. Whether that decline is a gradient or a step is an open question that the design is equipped to address: a step would show as a substantial quadratic or cubic component alongside the linear one, and its location would be identified by the adjacent-pair contrasts, which we expect to place the largest single drop at C–D. Nor do we assume the pattern is homogeneous across participants; a substantial random-slope variance would itself be informative, indicating that an average trajectory conceals distinct groups of respondents rather than describing a shared response. The expectation of decline is, in any case, consistent with survey evidence that public comfort is conditional on physician supervision [24,25,31]. For responsibility attribution, we expect the surgeon to be assigned the dominant share in low-autonomy scenarios [41], with a progressive migration toward the AI developer—and possibly a diffusion of responsibility across actors, indexed by falling Herfindahl concentration—as autonomy increases [44,45]. We expect the manipulation check (perceived AI control) to order the scenarios from A to D within each of the four presentation sequences, validating the experimental gradient independently of serial position, and we expect no scenario × sequence interaction. Should one nevertheless appear, the position-adjusted mixed-model estimate becomes the primary basis for interpreting H1–H3, and the magnitude of the order effect will itself be reported as a finding about the stability of vignette-based autonomy judgments. Given the design’s sensitivity (power of 0.99 against small within-subjects effects at ρ = 0.50, and 0.95 at ρ = 0.30, for the target sample), a null result for a primary hypothesis would place a tight upper bound on the size of any autonomy effect rather than leaving the question open; the pre-specified equivalence tests of Section 2.9.1 make that bound explicit rather than infer absence from non-significance [70]. The moderation hypothesis (H4) is powered only for medium-small interactions and will be interpreted with corresponding caution. Results will inform the ordering of public concerns along the assistance-to-autonomy continuum and identify which implementation configurations are publicly acceptable entry points for surgical AI in Romania.

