Trust in the healthcare system	B6	Likert 1–7	Covariate/exploratory moderator
Manipulation check (technical sophistication)	MAN2, per scenario (×4)	Likert 1–7	Design validation/covariate
Presentation sequence	SEQ	4 categories	Between-subjects design factor
Serial position of scenario	POS	1–4	Covariate (order, fatigue)

Abbreviations: DV, dependent variable; ACC, acceptability items; TRU, trust items; RSK, perceived-risk items; RES, responsibility items; MAN1 and MAN2, manipulation-check items; DIF1, perceived-difficulty item; ATT1 and ATT2, attention checks; CC_A–CC_D, comprehension checks; B1–B6, background items; G1–G4, general-attitude items; P1–P4b, preference items; D1–D7, demographic items; SEQ, presentation sequence; POS, serial position of the scenario; H1–H4, hypotheses 1–4.

**Table 5 healthcare-14-03030-t005:** Hypothesis-by-hypothesis analysis plan.

Hypothesis/Objective	Planned Test	Reported Coefficients
Manipulation validation	Mixed RM-ANOVA on MAN1 (autonomy within × sequence between) + polynomial trend contrasts; the intended ordering A → D expected within every sequence	*F*, corrected *df*, *p*, partial η^2^; ε(GG)
H1. acceptability and trust decline with autonomy	Mixed RM-ANOVA per composite, sequence as between-subjects factor (Greenhouse–Geisser) + orthogonal polynomial trend contrasts (linear, quadratic, cubic); post hoc dependent *t*-tests, Holm correction	*F*, corrected *df*, *p*, partial η^2^ (90% CI); pairwise dz (95% CI)
H2. perceived risk increases with autonomy	Mixed RM-ANOVA (autonomy within × sequence between) + orthogonal polynomial trend contrasts; post hoc dependent *t*-tests, Holm correction	*F*, corrected *df*, *p*, partial η^2^; pairwise *dz*
H3. responsibility migrates surgeon → AI developer	4 × 4 mixed ANOVA (scenario × actor within, sequence between), Greenhouse–Geisser; the scenario × actor interaction is the test of H3; repeated with a serial-position term	*F*, corrected *df*, *p*, partial η^2^; ε(GG)
Responsibility concentration	Normalized Herfindahl–Hirschman index (RES1–RES3) per scenario, compared by mixed RM-ANOVA (sequence between)	Mean HHI per scenario; *F*, *p*, partial η^2^
Moral–legal distinction	Mixed RM-ANOVAs on RES5 and RES6 across scenarios (sequence between); Holm correction within family	*F*, corrected *df*, adjusted *p*, partial η^2^

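### The manipulation check requires MAN1 to order all four scenarios, but the test Table 5 names for it does not test an ordering, and the ordering clause has no decision rule

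*Protocol article*

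**What the plan says.** Section 2.2 sets the criterion: "The manipulation is treated as valid only if MAN1 orders the scenarios as intended". Section 2.8 (item v) makes it mandatory in the pilot: "MAN1 scores must order the scenarios from A to D in both pilot arms", with 25 participants per arm. For the main study, Section 3 is softer: "We expect the manipulation check (perceived AI control) to order the scenarios from A to D within each of the four presentation sequences".

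The MAN1 row of Table 5 gives the test: "Mixed RM-ANOVA on MAN1 (autonomy within × sequence between) + polynomial trend contrasts; the intended ordering A → D expected within every sequence". Its reported coefficients are F, degrees of freedom, p, partial η² and ε. The H1 and H2 rows add Holm-corrected pairwise tests with dz; the MAN1 row does not.

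On the acceptability, trust and risk composites, Section 2.9.1 says that "the polynomial decomposition establishes departure from a straight line but cannot by itself locate the break", and uses the adjacent-pair contrasts A–B, B–C and C–D to do so. Section 2.2 describes Scenario C as one "whose decisional clause is functionally equivalent to Scenario B’s".

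**The concern.** The criterion concerns three adjacent steps. An omnibus F asks whether any of the four means differ, and a linear contrast asks whether they rise on average. Both can be highly significant when one or two steps are absent or reversed. Section 2.9.1 recognises this limit for the outcomes and supplies adjacent contrasts there, but MAN1 gets none.

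The profiles that slip through are realistic. MAN1 asks about AI control over the final decision. Section 2.2 says that Scenarios A to C all name the surgeon as decision-maker and that B and C are equivalent in this respect, so B = C, or even A = B = C < D, is a plausible result.

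The study intends to locate where acceptance breaks from the adjacent H1/H2 contrasts. Reading such a contrast as an autonomy effect requires that participants perceived an autonomy step there. A significant trend could be reported as validation when they did not. In the other direction, a strict reading of the ordering in small arms could fail a sound manipulation through sampling error.

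**Working it through.** **Inputs.** N = 300 in four equal sequences (75 each) and a pilot of 2 × 25 (Sections 2.1, 2.5, 2.8). Section 2.5 works "at a two-tailed significance threshold of α = 0.05 and a target power of 1 − β = 0.80" and starts from "Assuming a correlation between repeated measurements of ρ = 0.50", with 0.30 as the conservative value. The protocol gives no MAN1 gaps, so these are varied, in units of the SD of a single rating, with normal scores and compound symmetry. At ρ = 0.50 a gap of 0.2 SD equals dz = 0.20. Ranges below run over ρ = 0.30 to 0.50.

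**The plan's own figures first.** With λ = f²·N·4/(1 − ρ) and df = 3 and 3(N − 1), at f = 0.10:
- N = 138, ρ = 0.50: λ = 0.01 × 138 × 4 / 0.50 = 11.04, power 0.80.
- N = 193, ρ = 0.30: power 0.80.
- N = 300: power 0.991 (ρ = 0.50) and 0.949 (ρ = 0.30).

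These match Sections 2.5 and 3. The protocol states no pass probability for the MAN1 check.

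**What the trend sees when only D differs.** Take means (0, 0, 0, d). The sums of squares per participant are:
- linear (−3, −1, 1, 3): (3d)²/20 = 0.45d²
- quadratic (1, −1, −1, 1): d²/4 = 0.25d²
- cubic (−1, 3, −3, 1): d²/20 = 0.05d²

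The total is 0.75d², so the linear share is 60%, the quadratic 33% and the cubic 7%.

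**Chance of a significant test at N = 300.** The noncentrality of the linear t is (Σcμ)/√(20(1 − ρ)) × √300. For d = 0.3, Σcμ = 0.9, giving 0.9/√14 × √300 = 4.17 at ρ = 0.30 and 0.9/√10 × √300 = 4.93 at ρ = 0.50.

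| True MAN1 means (SD) | Linear trend | Omnibus |
|---|---|---|
| 0, 0, 0, 0.2 | 79–91% | 87–96% |
| 0, 0, 0, 0.3 | 98–100% | about 100% |
| 0, 0.5, 0.5, 1.5 (B = C) | about 100% | about 100% |
| 0, 0.5, 0.4, 1.4 (C below B) | about 100% | about 100% |

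**The ordering clause, read as order of sample means in every arm.** True equal gaps:

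| Gap (SD) | Main study, 4 × 75 | Pilot, 2 × 25 | Pilot pooled, 50 |
|---|---|---|---|
| 0.2 | 39–59% | 21–31% | 67–77% |
| 0.3 | 84–95% | 50–65% | 89–95% |
| 0.4 | 98–99.7% | 75–87% | 98–99% |
| 0.5 | above 99% | 90–96% | above 99% |

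If B = C with large steps on either side, each arm is in order half the time: (1/2)⁴ = 6.25% for four sequences, while the trend passes about 100%. If only D differs, three tied means fall in order one time in six: (1/6)⁴ = 0.08%.

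**All three adjacent contrasts positive and significant, two-sided 0.05, N = 300.** Pass probability is about 0% if only D differs, 2–3% if B = C, about 52–81% for three true steps of 0.2 SD and 98–99.6% for steps of 0.3 SD.

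**The case against.** A reader might infer that the protocol accepts a significant trend as validation, so that the check establishes no gradient at all. The text does not support that. No section says a significant omnibus F plus trend is sufficient, and the same Table 5 cell adds the ordering within every sequence. If that clause were enforced on means, it would almost never pass a profile in which only D differs (0.08%) and would rarely pass B = C (6%).

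A reader might equally infer that the main-study check will often fail by chance. That too is limited. The protocol does not say that raw means are compared, ordering within sequences is described there as expected rather than required, and chance failure is rare once gaps reach about 0.4 SD. Only the pilot wording is mandatory.

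It can also be said that consistency across sequences is already covered. It is: the named mixed ANOVA yields the scenario × sequence term on MAN1, and Section 2.9.2 (ix) adds sequence-specific profiles.

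Finally, the decision rule could sit in the separate analysis plan mentioned under Data Availability. That would excuse a missing detail. It does not excuse the mismatch here, because the article fixes both a criterion and a test that does not address it, and Section 2.12 labels the manipulation checks confirmatory.

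**Conclusion.** The concern holds in limited form. The test named for MAN1 does not test the criterion set in Section 2.2. The ordering that accompanies it has no rule for sampling error, and the two can give opposite answers: about 100% against about 6% when B = C. The chance-failure problem is substantial in the pilot arms of 25 up to gaps of about 0.3–0.4 SD; in the main study it is confined to gaps of roughly 0.2–0.3 SD or less.

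All pass rates rest on assumed MAN1 gaps, normal scores, compound symmetry and ρ between 0.30 and 0.50. That polynomial trends do not establish an ordering does not depend on these assumptions.

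**What to change.** - **Main study.** Add the three adjacent contrasts (B−A, C−B, D−C) to the MAN1 row of Table 5, pooled over sequences with sequence in the model. Test them two-sided at 0.05, in line with Section 2.9.2. Declare the ordering shown only if all three are positive and significant. Because all three must succeed, no multiplicity correction is needed.
- **Interpretation.** Where a step is not shown, do not interpret the matching adjacent H1/H2 contrast as an autonomy effect.
- **Consistency.** Judge it by the already planned MAN1 scenario × sequence term, and report the sequence profiles descriptively.
- **Pilot.** Judge the order of the MAN1 means on the 50 participants pooled over both arms, and report the adjacent differences with 95% confidence intervals. Do not count a failure only when a step is reversed beyond its interval: such a rule passes about 93% of pilots with no differences at all.

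The cost is three contrasts on data already planned and a few sentences, before pre-registration. The main-study rule is stricter than a trend test: with three true steps of 0.2 SD it would be met in only about 52–81% of studies. The pooled pilot order is a screen, not proof: with B = C it still holds about half the time, so the intervals must be read with it.
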